#### 3.3.3. Methods Considering Missing, Unused or Invalid Data

The statistical nature of missing data will be studied using sensitivity analysis. It will also be used to choose the most appropriate approach for the imputation of missing data: maximum bias (e.g., last observation carried forward, baseline observation carried forward) or estimation proposed by Verbeke and Molenberghs for repeated data. 

Particular attention will be paid to study of the adherence of participants to the intervention. Participants abandoning will be studied using this parameter as a censored data, which will involve the use of Kaplan–Meier to estimate it and log-rank for the comparison between groups. 

## 4. Discussion

The World Health Organization defines health as “not merely the absence of disease or infirmity but a state of complete physical, mental and social well-being” [56]. In fact, the role of well-being at work plays a major role in social well-being [57]. HCW are particularly at risk [4,5,6,7,8]. Moreover, NHCW staff of hospitals can also be at risk [11,12], with working environment described as the main risk factor [13]. Indeed, the medical staff, especially those working in emergency departments are exposed to psychosocial risk factors because of the type of work they do [58,59]. Moreover, the COVID-19 pandemic has worsened the situation all around the world [60,61,62]. In general, HCW are confronted with the death of patients and the distress of their families [63]. 

Sophrology is a mind–body method used as a therapeutic technique or experienced as a philosophy of life. It helps to regain a state of well-being and to activate all physical and psychological potentials in order to acquire a better knowledge of oneself [14]. NLP is a set of communication and self-transformation techniques that focuses on reactions rather than on the origins of behaviors [15]. NLP combined with sophrology proposes above all to mobilize the resources of the unconscious.

This protocol seems particularly interesting for the University Hospital (CHU) of Clermont-Ferrand because it is one of the three CHU in France with more than 10% absenteeism, and the first CHU for duration of sick leave. By proposing sophrology to professionals at risk of suffering at work, this study design will allow us to observe a short-term effect (the first 3 months) and a long-term effect (4 months follow-up). This study will provide important data about the benefits of sophrology and NLP for workers at risk of stress-related disorders.

Articles related to this study protocol will follow the CONSORT recommendations for reporting randomized trials.

### Potential Limitations

The psychological questionnaires in this study are self-assessed and may suffer from a bias of auto-evaluation. For the study, participants need to attend 6 to 8 sophrology sessions and one visit per month for 7 months, which might seem demanding. Therefore, to make sure that participants will complete the protocol, one person will oversee the participants’ follow-up. We are not immune to a confusion bias. For example, observed changes may be produced by other factors than NLP, such as organizational changes during the intervention period. However, we tried to minimize this risk. First of all, healthcare professionals or volunteers from healthcare institutions will be very diverse and will not belong to a single department. In addition, the RCT design will also limit the risk of confusion bias as participants will be both compared to a control group with deferred intervention (intergroup comparison) and their own control (intragroup comparison). Blinding assessment is impossible considering the nature of the intervention. However, outcomes will be collected by a research assistant independently from the randomization process or the intervention to minimize contamination of the intervention group.

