### 2.2. Study Settings

We will recruit any HCW or any NHCW from a healthcare institution (such as CHU of Clermont-Ferrand, other hospitals, clinics, retirement homes, EHPAD, etc.), who will be randomized in two groups: (i) the intervention group will have a longitudinal follow-up of seven months in total (a control period of 1 month, then 6 to 8 sophrology sessions during two months, then a 4-month follow-up); (ii) the control group will have a differed intervention (longitudinal follow-up of seven months in total beginning by a control period without intervention of 3 months, then 6 to 8 sophrology sessions during two months, then a 2-month follow-up).

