### 2.4. Eligibility Criteria

The inclusion criteria are to be an HCW or an NHCW from a healthcare institution (such as CHU of Clermont-Ferrand, other hospitals, clinics, retirement homes), between 18 and 65 years, with a stress greater than or equal to 50 on a visual analogue scale (VAS) of stress, to be able to give an informed consent to participate in research and to be affiliated with a Social Security scheme. The exclusion criteria are to have psychiatric, cardiovascular (heart failure, arrhythmia, etc.), hepatic (liver failure, etc.), renal (kidney failure, etc.), or endocrinological diseases (diabetes, etc.) judged by the investigator to be incompatible with the study because they may interfere with the measurements. Persons who are non-affiliated to a health insurance or protected persons (minors, pregnant women, breastfeeding women, guardianship, curatorship, deprived of freedoms, safeguard of justice) or persons who refuse to participate are not included.

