### 2.6. Outcomes

The main outcome is heart rate variability change between M1 and M3. HRV will be measured using Zephyr™ BioHarness™ BT (Zephyr Technology, Annapolis, MD, USA). The main secondary outcomes are subjective (questionnaires: perceived stress, personality and perception of work, etc.) and objective markers of stress (biomarkers of stress such as other measures of the activity of the autonomic nervous system, DHEAS, cortisol, etc.). All outcomes are presented in Table 1.

For both groups (interventional and control groups): (i) heart rate variability, skin conductance and saliva biomarkers will be assessed once by week during the intervention period (6 to 8 sophrology sessions) and once by month the rest of the time; (ii) the short questionnaire will be collected once a week during the whole protocol (1–2 min); and (iii) the long questionnaire will be assessed only 5 times: at baseline (M0), month 1 (M1), month 3 (M3), month 5 (M5), and the end of the protocol (M7).

Outcomes will be collected by a research assistant without any link with the randomization process nor the intervention. The independence is necessary to minimize contamination of the intervention group, particularly in study designs which cannot be blinded.

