#### 3.3.2. Analyses for the Secondary Outcomes

Randomized groups comparison will be carried out (i) as aforementioned for continuous secondary endpoints and (ii) for categorical endpoints using Fisher exact tests or chi-squared. The results will be introduced using median difference and 95% confidence intervals estimated using quantile regression model for non-Gaussian data. The results will be presented using absolute differences and 95% confidence intervals for categorical parameters. The multivariable analysis related to dichotomous endpoints will be generalized linear mixed model, with logit link function, and center as random-effect. The results will be expressed with of relative risks and 95% confidence intervals.

Longitudinal data will be analyzed using random-effects regressions, modeling between and within participant effect, as random-effect, in addition to session effect. These analyses will concern (i) within groups comparisons between and M0 to M7 by randomization group and (ii) between groups: comparisons at M5 and then between M0 and M7). For between groups comparisons, the following fixed effects will be studied: randomization group, time-points evaluation and their interaction. 

Subgroup analyses will be conducted to explore potential influence of sex, occupation, stress at baseline, and previous sophrology experience on the primary outcome. Interaction terms in the regression models will be used to test for heterogeneity of effect between subgroups.

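### The within-person M0 to M7 comparison is credited with limiting confounding, but it cannot remove time-varying factors, and entry at stress VAS 50 or more makes a no-effect fall in stress likely

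*Protocol article*

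**What the plan says.** Eligibility (section 2.4) admits workers "with a stress greater than or equal to 50 on a visual analogue scale (VAS) of stress". Stress then returns as an outcome. Section 2.6 states: "The main secondary outcomes are subjective (questionnaires: perceived stress, personality and perception of work, etc". Table 1 adds weekly 100 mm scales that include stress at work and stress at home.

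Section 3.3.2 plans, for the longitudinal data, "within groups comparisons between and M0 to M7 by randomization group", together with between-group comparisons at M5 and from M0 to M7. The end of the Introduction attaches the same comparisons to the secondary objectives, including the intervention's effects and its long-term effects. Section 3.3 sets two-sided p < 0.05 for all tests and calls most secondary analyses exploratory.

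Potential Limitations raises the possibility that something other than the programme produces the changes and gives organisational change as its example. It answers that "the RCT design will also limit the risk of confusion bias as participants will be both compared to a control group with deferred intervention" "and their own control (intragroup comparison").

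The control arm has a period "beginning by a control period without intervention of 3 months, then 6 to 8 sophrology sessions during two months, then a 2-month follow-up" (section 2.2). The primary outcome lies elsewhere: "The main outcome is heart rate variability change between M1 and M3", compared between arms.

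**The concern.** Two separate problems meet in the within-group comparison.

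- **Time-varying factors.** A before-after comparison cancels whatever is constant in a person. A reorganisation, a seasonal workload pattern or the passing of a difficult period coincides with the intervention and stays in the estimate. The stated safeguard therefore does not answer the threat it is set against.
- **Regression to the mean.** People enter because a stress reading is high. Later readings are expected to be lower on average, for stress and, more weakly, for self-reports correlated with it. The bias points towards benefit.

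At stake is what the secondary results can support. The control arm is treated between M3 and M5, so no untreated arm covers M3 to M7, and the M5 comparison sets two treated arms side by side. The long-term objective then has little but within-arm change to lean on, and a significant fall from M0 to M7 could be read as effect and persistence.

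**Working it through.** **Part 1, no arithmetic needed.** Potential Limitations names a factor that changes during the study. A within-person difference removes only what does not change. Stable differences are already balanced in expectation by randomisation. Own-control therefore adds no protection against the named threat; the concurrent randomised arm does provide it, up to M3.

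**Part 2, possible size of regression to the mean.**

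*Inputs from the protocol article:* entry cut at 50 (section 2.4); 85 per arm (section 3.1); 5% two-sided (section 3.3). The 85 reproduces for effect size 0.5 and 90% power (noncentral t power 0.8999), and 85/(1 − 0.15) = 100 matches the planned inclusion.

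*Assumptions, because the article gives no VAS distribution:* source mean 40 to 50, SD 20 to 25, M0 to M7 correlation r of 0.6 to 0.8, a normal model, the entry VAS serving as M0, and the same item as outcome.

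*Formulas with zero effect:*

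- a = (50 − mean)/SD, and λ = φ(a)/(1 − Φ(a))
- expected fall = (1 − r) × SD × λ
- variance of change = (1 − r)² × SD² × (1 + aλ − λ²) + SD² × (1 − r²)
- chance of significance: noncentral t, paired test, n = 85

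*Smallest corner* (mean 50, SD 20, r = 0.8): a = 0, λ = 0.798, fall = 0.2 × 20 × 0.798 = 3.2 mm.

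*Largest corner* (mean 40, SD 25, r = 0.6): a = 0.4, λ = 1.069, fall = 0.4 × 25 × 1.069 = 10.7 mm.

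| Mean | SD | r | Fall (mm) | SD of change | P(significant), one arm |
|---|---|---|---|---|---|
| 40 | 20 | 0.6 | 9.1 | 16.5 | 0.999 |
| 40 | 20 | 0.8 | 4.6 | 12.2 | 0.927 |
| 40 | 25 | 0.6 | 10.7 | 20.7 | 0.997 |
| 40 | 25 | 0.8 | 5.3 | 15.2 | 0.892 |
| 50 | 20 | 0.6 | 6.4 | 16.7 | 0.936 |
| 50 | 20 | 0.8 | 3.2 | 12.2 | 0.661 |
| 50 | 25 | 0.6 | 8.0 | 20.9 | 0.936 |
| 50 | 25 | 0.8 | 4.0 | 15.3 | 0.661 |

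With standard error = SD of change/√85, the fall is about 2.4 to 5.1 standard errors.

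*Wider assumptions* (mean 40 to 60, r = 0.5 to 0.9) give a fall of 1.0 to 13.4 mm and an 18% to >99% chance of significance.

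*Simulation* (4,000 trials; mean 50, SD 20, r = 0.6, no effect): the within-arm test rejects in 93.9% of trials, and the randomised comparison of change rejects in 4.8%.

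*If M0 is a separate reading after screening:* fall from M0 to M7 = (r between screening and M0 − r between screening and M7) × SD × λ. It is 0 if the two correlations are equal. It is about 1 to 8 mm if the correlation decays by 0.1 to 0.3 (mean 40 to 60, SD 20 to 25).

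**The case against.** Much of the case on the other side is fair.

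- **The entry reading may not be M0.** Section 2.5 describes an inclusion visit, possibly by teleconsultation, with up to 8 days' reflection and a baseline measure that can fall later. Part or all of the fall could then occur before M0. This stands, so zero belongs in the range.
- **The entry item may not be an outcome item.** Entry uses a VAS of stress, while the weekly scales ask about stress at work and at home. With different items the fall is diluted by an unknown correlation. This stands.
- **The within-group plan is loosely worded.** The phrase in section 3.3.2 seems to lack a word, and the method is a random-effects regression over time points, not a bare paired test. This stands, but a within-arm time effect from such a model carries the same bias.
- **Own-control could mean the untreated run-in periods** of one and three months in section 2.2. The limitations section does not tie it to M0 versus M7. However, the only within-group window that the analysis section names is M0 to M7.
- **Most secondary analyses are called exploratory.** True, but nothing says that within-group changes carry no effect claim, and the limitations section credits them with limiting bias.

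A reader might also infer that the plan rests on own-control, that both arms would certainly show significant improvement, or that own-control has no value. The documents support none of these. The randomised comparison is named first in the same sentence. At the weakest corner of the table the chance for both arms is about 0.661² = 0.44. Own-control does remove stable personal differences.

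**Conclusion.** The point holds for secondary within-group results. Listing the intragroup comparison as a protection against confounding is wrong for time-varying factors, including the example the article gives, and this needs no numerical assumption. Selection at stress VAS 50 or more makes a no-effect fall in stress and correlated self-reports likely.

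The size is conditional on the assumed VAS distribution, on the entry VAS being M0, and on the same item being the outcome. On those terms it is 3.2 to 10.7 mm, with a 66% to >99% chance of significance in one arm of 85. With a separate M0 it is smaller and may be zero.

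It would be a mistake to extend this to the main result: the primary HRV contrast from M1 to M3 is between randomised arms, which regression to the mean affects alike. Severity is minor to moderate.

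**What to change.** 1. In Potential Limitations, drop own-control as a protection against time-varying confounding. Add regression to the mean after threshold entry as a limitation.
2. In section 3.3.2, state that within-group M0 to M7 changes are descriptive and carry no claim of effect or persistence.
3. Base effect statements, including those on stress, on the randomised contrast up to M3.
4. Wherever a within-arm change is reported, show beside it the waiting-list arm's untreated M0 to M3 change. It reflects regression to the mean and time trend together and is already collected. It is only a partial benchmark, because it covers three of the seven months.

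The cost is wording and one table column, with no new data, visits or participants. The price is fewer within-group p-values, and long-term persistence can only be described.

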#### 3.2.1. Heart Rate Variability (HRV)

A Zephyr™ BioHarness™ BT (Zephyr Technology, Annapolis, MD, USA) will record HRV parameters. The Zephyr™ BioHarness™ BT is a heart rate transmitter belt simply positioned on the chest, with a 26 h recording time, a beat per minute within a 25–240 range, and respiratory rate within a 3–70 range. The aim will be to demonstrate that is it possible to detect anxiety using this easy to use and cheap device. Anxiety could also be detect using the respiratory rate. In addition, the Zephyr™ BioHarness™ BT will also measure the trunk’s movements with a 3-Axis accelerometer. Recommendations of the European Society of Cardiology and the North American Society (Task Force) will be followed to examine the HRV data. Time and frequency domains will be used to explore HRV. [50]. We will also apply the methodology developed by our team [51].

We will visually check the premature beats who will be automatically reject. Several element will be analyzed in time domain: R–R intervals and their standard deviation, the number of adjacent N–N differing by more than 50 ms divided by the total number of N–N inter-vals (pNN50) and the square root of the mean squared difference of successive R–R intervals (rMSSD). The pNN5 and rMSSD are related with high frequency (HF) power and therefore to parasympathetic activity. High (0.15–0.4 Hz) and low (0.04–0.15 Hz) frequency power will be examine in the spectral domain. HF is the principal efferent parasympathetic (vagal) activity to the sinus mode, LF is an indicator for both parasympathetic and sympathetic functions. The variations of thermoregulatory mechanisms, activity of the renin–angiotensin system and the function of peripheral chemoreceptors are partially reflects by very low frequency (VLF, 0.003–0.04 Hz). Normalized units (nu), corresponding to the relative value of each power component in proportion to the total power minus the VLF component, will also be used to assessed LF and HF. Thus, the best sympathetic and parasympathetic activity seems to be represented by LFnu and HFnu, respectively. The LF/HF ratio, that is, the sympathovagal balance, will also be calculated (Table 2) [52].

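### Blinded assessment is called impossible, but that is true only of participants and therapist: the visual beat check behind the primary HRV endpoint can be masked at low cost

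*Protocol article*

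**What the plan says.** Four places in the protocol article bear on this.

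- **Section 4, Potential Limitations:** "Blinding assessment is impossible considering the nature of the intervention". No endpoint or processing step is excepted. The safeguard that follows is that "outcomes will be collected by a research assistant independently from the randomization process or the intervention".
- **Section 2.6, Outcomes:** the primary endpoint is fixed as "The main outcome is heart rate variability change between M1 and M3". The same safeguard appears: "Outcomes will be collected by a research assistant without any link with the randomization process nor the intervention". Its purpose is given as "The independence is necessary to minimize contamination of the intervention group, particularly in study designs which cannot be blinded".
- **Section 3.2.1, HRV:** the signal comes from a chest belt "with a 26 h recording time, a beat per minute within a 25–240 range", which also records respiratory rate and trunk movement. On processing, the text says: "We will visually check the premature beats who will be automatically reject".
- **Section 3.3, Data Analysis:** the analyses are to be carried out before the randomisation code is broken. HRV reading is not mentioned there.

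Pseudonymous coding is described in section 2.3, for questionnaire results only.

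**The concern.** A session-based group programme cannot be hidden from those who attend it or lead it. Reading a recording taken by a device is a separate act, and nothing about sophrology prevents a reader from working on a file without knowing whose it is. The blanket statement therefore rules out a protection that is available for the trial's own primary endpoint.

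The stated safeguard does not fill the gap. Independence from randomisation and from the intervention is not blindness, and collecting a recording is not the same as processing it. The stated aim, limiting contamination, is also a different problem from detection bias.

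What is at stake is the M1 to M3 contrast. rMSSD is built from successive beat differences, so whether a premature beat is kept can change its value. If a reader knows arm or visit and is slightly stricter on one side, that difference in strictness enters the comparison as bias, and a larger sample does not remove it.

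**Working it through.** **1. The plan's own figure.** The document gives no number for reading bias, so the only figure to reproduce is the sample size that sets the scale of the primary comparison. Inputs from section 3.1: effect size 0.5, two-sided 5%, power 90%.

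n per group = 2 × (1.960 + 1.282)² / 0.5² = 84.1, rounded up to **85**, as stated. The noncentral t gives 85.03 per group, with power of 89.99% at 85. The 100 per group to be included corresponds to 1 − 85/100 = 15% loss. The change proposed here leaves these numbers as they are.

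**2. The passages side by side.**

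- Reason for not blinding: the nature of the intervention. This reaches participants and therapist.
- Primary endpoint: HRV change, recorded by a belt and then processed. Processing after recording is inferred from the recorder and the later check; storage of HRV files is not stated.
- Human step in processing: a visual check of premature beats, combined with automatic rejection. The share of manual decisions is not given.
- Who does the check, and whether masked: not stated.
- Analysis before code break: presupposes some masking of arm, which the blanket statement does not allow for. The mixed model in section 3.3.1 also lists the number of sessions completed as a possible covariate. By section 2.2 the waiting-list group has no sessions between M1 and M3, so that variable could show the arm to an analyst.

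**3. How far one beat can move rMSSD (assumed values).** A beat k ms early with a full compensatory pause gives successive differences of about −k, +2k and −k. It adds k² + 4k² + k² = 6k² to the sum of squares. The assumptions, none of them from the document, are a true rMSSD of 30 ms and 70 beats per minute, so N = 350 in 5 minutes and N = 4,200 in one hour.

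rMSSD = √[(N × 30² + 6k²) / N]

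| Recording | k (ms) | Sum of squares | rMSSD (ms) | Rise |
|---|---|---|---|---|
| 5 min | 250 | 315,000 + 375,000 = 690,000 | 44.4 | 48% |
| 5 min | 150 | 315,000 + 135,000 = 450,000 | 35.9 | 20% |
| 1 hour | 250 | 3,780,000 + 375,000 = 4,155,000 | 31.5 | 5% |
| 1 hour | 150 | 3,780,000 + 135,000 = 3,915,000 | 30.5 | 2% |

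**4. What a systematic shift would do (assumed values).** Suppose there is no true effect, and differential reading shifts the group difference by b standard deviations. With a = b × √(n/2), the two-sided 5% test rejects with probability Φ(a − 1.96) + Φ(−a − 1.96).

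| b (SD) | n = 85 per group | n = 100 per group |
|---|---|---|
| 0.05 | 6.2% | 6.4% |
| 0.10 | 10.0% | 10.9% |
| 0.20 | 25.6% | 29.3% |
| 0.30 | 49.8% | 56.4% |

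Nothing in the document says which value of b, if any, is realistic.

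**The case against.** The strongest reply is that this is one sentence in a limitations paragraph. The sentence after it concerns who collects outcomes, so it may be about contact between assessor and participant and not a rule against masking file processing. Rejection of beats is called automatic, under published recommendations and a method of the team's own, so little discretion may remain. An article may also leave file handling to the full protocol.

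Part of this stands, and it marks where a reader might infer too much:

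- **That the trial gives up all masking.** Section 3.3 foresees analysis before code break, so some masking is intended.
- **That the primary endpoint rests on manual editing.** The text pairs a visual check with automatic rejection, so the check is a part of the processing and its weight is unknown.
- **That the reader will recognise the arm from the schedule.** Recordings are made at each session during the intervention period and monthly otherwise, so a full set of dated files could reveal the arm. The document does not say who reads, what that person sees or how files are labelled.
- **That the saliva assays carry the same problem.** They are secondary outcomes, and section 2.2.3 describes no subjective reading step.

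What does not stand is the appeal to condensation. The article does not merely stay silent about masking. It asserts that masking is impossible, and for the beat check that is wrong.

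**Conclusion.** The point holds in a limited form. The impossibility applies to participants and therapist. It does not apply to the visual check of premature beats, which can be masked cheaply, and neither the independent collector nor the statement about code break is said to cover that check.

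The size of any bias cannot be derived from the documents. It is tempting to take the 20 to 48% rise in rMSSD as its size, but that would be unsupported. It describes one participant, one retained beat and an assumed 5-minute segment, while section 3.2.1 says premature beats are rejected. Over an assumed hour, the length of a session in section 2.2.1, the rise is about 2 to 5%, and how often such decisions would differ by arm is unknown. The rejection rates in the working likewise depend wholly on the assumed shift. The case for change is therefore that an inexpensive safeguard has been declared unavailable, not that the result is shown to be biased.

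**What to change.** - In Potential Limitations, limit the sentence to participants and therapist.
- In section 3.2.1, state that premature beats are checked and rejected by one fixed rule, on HRV files that each carry a random code without arm, visit or date.
- Withhold the respiration and movement traces from the reader. Recordings made during sessions could show the arm through them even when file names are coded.
- State that files are linked to arm and visit only after the edited HRV data are locked.
- Reconcile Potential Limitations with section 3.3, saying which steps precede code break and whether HRV reading is among them.

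Coding the saliva tubes in the same way is optional and secondary.

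**Cost:** low, but not nil. It needs a recoding step and a code-holder among existing staff who does not edit the recordings, plus a short change of wording. It adds no visit or measurement and does not alter the sample size.
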